##### AE management

During participant recruitment, individuals will receive a suicide risk assessment (33). Individuals with high suicide risk will be excluded from the study. Those with a low to moderate risk will be included, their thoughts will be assessed at every group meeting and care givers will be asked to keep close watch on the affected individual. If suicidal thoughts are still present after 4 sessions of GSP-IAC or IAC only these individuals will be referred to a mental health worker in the Kitgum Mental Health Clinic. Details of the trial risk management plan are provided as Supplementary material.

#### Retention

In order to maximize adherence to intervention sessions and retention, lay health workers (LHWs) who facilitate the group sessions and the HIV care providers who provide the adherence counselling will be provided with a financial incentive as an appreciation of their commitment to the project. For participants who miss group sessions, the LHWs will be facilitated to make home visits to re-engage them.

#### Study measures and data collection schedule

Assessments of study measures will be conducted at baseline, at the end of the interventions (2 months), 6 and 12 months after the interventions. Table 2 (34–42) summarizes the study measures.

**Table 2 T2:** List of study measures and data collection schedule.

Study Measures	Instrument	Data collection schedule(months)			
		**0**	**2**	**6**	**12**
Socio-demographic variables	Standardized Demographic Questionnaire	✓			
**Primary outcomes**					
Indicators of feasibility	The proportion of eligible participants who take up either intervention (**Reach**) The proportion who attended all 8 sessions of either intervention (**Dose delivered**) The proportion who are lost to follow-up (**Attrition**) will be determined from the attendance registers		✓		
Indicators of acceptability	A 9-item questionnaire (34) will assess participant's satisfaction, the group facilitators’ knowledge and attitudes, and the participant evaluation of the intervention's ability to reduce stress		✓		
Adherence to ART	One question “During the past three weeks, on how many days have you missed taking all your medication doses?”	✓		✓	✓
Viral Load	Medical charts of study participants	✓		✓	✓
**Secondary outcomes**					
Fidelity	A semi-structured self-administered questionnaire completed by group facilitators will assess whether or not the interventions were delivered as planned.		✓		
Contextual influences	A semi-structured self-administered questionnaire completed by group facilitators will assess any facilitators or barriers to intervention delivery that they observed during group sessions.		✓		
Depression symptoms	The 25-item revised child and adolescent anxiety and depression scale (RCADS-25) will be used to assess anxiety and depression symptoms. Although it has not been validated in Ugandan populations, its items have face validity. It has been widely used in Europe North and South America with internal reliability ranging from 0.87 to 0.90 (35, 36), a high sensitivity of 90% and specificity of 75% (37). RCADS scores will be modeled as a continuous variable.	✓	✓	✓	✓
Suicide risk	Suicide risk will be assessed using the 10-item Patterson suicide risk assessment tool. Its validity and reliability have not been evaluated in Uganda. Due to its brevity and face validity it has been used in both adults and young people in Uganda (33)	✓	✓	✓	✓
Post-traumatic stress symptoms	The 17-item Clinician-administered post-traumatic stress disorder scale for children and adolescents (CAPS-CA) will be used to assess PTSD symptoms. Although it has not been validated in Ugandan populations, its items have face validity The tool has been widely used in Europe North and South America with internal reliability ranging from 0.83 to 0.87 (38–41), a high sensitivity of 90% and specificity of 75%. CAPS-CA scores will be modeled as a continuous variable.	✓	✓	✓	✓
Social support	The child and adolescent social support scale (CASS) will be used to assess social support. Although it has not been validated in Ugandan populations, its items have face validity. It's internal consistency reliability coefficient ranges from 0.87 to 0.94) in studies conducted in Europe (41).	✓	✓	✓	✓
Stigma	The 8-item HIV stigma scale for children (HSSC-8) will be used to assess stigma. It has internal consistency reliability coefficient of 0.81 (42).	✓	✓	✓	✓

#### Sample size justification

The goal of this pilot trial is to test trial procedures and processes and to get estimates of parameters for the main trial sample size calculation (43). Therefore, the sample size formulae which are used for main treatment assessments are not usually applicable to pilot trials. Therefore, we applied the sample size flat rules of thumb proposed by Sim and Lewis (44) and chose a sample size of 60 per treatment arm.

#### Determining cost-effectiveness

We will determine the cost-effectiveness of the GSP intervention compared to the standard of care IAC. To facilitate this, our proposed costing perspective is the “societal perspective”, which will include intervention costs, costs related to the use of other healthcare resources, as well as lost time to attend the intervention.” We will develop a questionnaire to collect information on the use of other healthcare resources that can be impacted by the intervention such as got insurance medical visits, ambulatory care, mental health-related medication, etc.

Data on costs involved in delivering the two models will be determined and these will then be compared to the targeted outcomes of the two delivery models. The main primary outcomes of the study—ART adherence and Viral Load, will be utilized. Important to note, however, is that costs of research and research related activities shall not be included in determining cost-effectiveness. Additional data on economic costs—costs of lost time, for categories of participants, including voluntary unpaid participants, costs of additional workload, etc., in the study shall be explored, using shadow pricing methods. Costs will be identified from project documents and accountabilities. Additional costs will be generated from literature in case they may not be available in the available project documents. Major costs for services and other procurements shall be based on reimbursement contracts, and in some circumstances market rates when they were procured. Other databases including Uganda Bureau of Statistics (UBOS) shall be used to generate relevant data for use in cost-effectiveness analysis.

### Statistical analyses

#### Qualitative data

Interview transcripts from the FGDs will be reviewed for accuracy, translated into English and transcribed. Atlas.ti qualitative data analysis software will be used for coding and thematic analysis (45). The interview data will be initially coded according to a number of themes that correspond to the focus questions. The codes will be used to construct matrix displays based on the co-occurrence of codes and the two treatment groups. The resulting matrix display will provide both the frequency of responses and the detailed content of responses, allowing us to assess how often responses will vary between the two treatment groups. Inter coder reliability will be determined.

#### Quantitative data

For the quantitative data, we will do bivariate analyses with *χ*^2^ tests and independent two-sample *ttests* to compare categorical and continuous baseline demographic and psychosocial variables between study groups respectively. Similarly, we will also do bivariate analyses to compare these variables between those who had completed all sessions (completers) and those who had not (non-completers). Although randomisation to GSP and GHE will be done at the individual level, study participants will receive their respective interventions in groups (clusters). Since individuals within a cluster are likely to be correlated, we will use cluster-level analyses to make allowance for intra-cluster correlation.

We will apply ttests to cluster-level summaries, which is a robust method of analysis for cluster data (46). Specifically, we will use the STATA collapse command to obtain cluster-level summaries of the study outcomes from data on individual participants. This procedure will reduce the data from 120 individual participants to 12 groups. We will then use the *clttest* command to compare cluster means across treatment groups.

To do an intention-to-treat analysis, we will impute missing values with several imputations. We will construct five imputed datasets with the multivariate normal model assuming that data were missing at random. The participants complete baseline data will be used to create the multiple imputation datasets.

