**Methods:**

We recruited 120 young people with HIV, aged 10–18 years, who had non-viral suppression 6 months after initiating first-line anti-retroviral therapy (ART) from community based HIV clinics in Kitgum district, northern Uganda. Participants were randomly assigned to receive GSP plus IAC (*N* = 60) or IAC alone (*N* = 60). Primary outcomes will be indicators of feasibility and acceptability as well as preliminary effectiveness of GSP in improving ART adherence and viral suppression analysed by intention to treat using cluster-adjusted t tests and permutation tests. Secondary outcomes will be measures of depression, anxiety and cost-effectiveness.

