The goal of this paper is to describe the protocol for the evaluation of the feasibility, acceptability and preliminary effectiveness of group support psychotherapy in improving ART adherence and viral suppression among HIV positive young people in Uganda. In the preparatory phase of this trial, we aim to conduct community-based participatory qualitative research to obtain information on the potential usefulness of group support psychotherapy in addressing the psychosocial challenges that impact adherence to anti-retroviral therapy and viral suppression among young people with HIV in northern Uganda.

In the trial phase of this study, the primary objective will be to assess the feasibility, acceptability and preliminary effectiveness of GSP in promoting ART adherence and viral suppression among HIV positive young people with non-viral suppression 6 months after initiating first-line ART at community-based HIV clinics in Kitgum district. Secondary objectives will include exploration of indicators of causal mediating processes and contextual influences, exploration of whether or not improvement in psychosocial challenges including depression, posttraumatic stress symptoms, suicide risk, social support, and stigma mediate or modify the effect of GSP on ART adherence and viral suppression, exploration of whether or not promotion of adherence through group support psychotherapy translates into better viral load suppression compared to standard care with intensive adherence counseling (IAC) and exploration of the cost-effectiveness of GSP to improve viral load suppression among HIV positive young people taking anti-retroviral therapy.

We hypothesize that in comparison to the control intervention, GSP will demonstrate better feasibility, acceptability and better preliminary HIV treatment outcomes and better cost-effectiveness. The primary end point will be 6 months after the end of the intervention. Data will be used to design a definitive cluster randomized trial which will test the hypothesis that group support psychotherapy promotes better ART adherence and viral suppression than standard care with intensive adherence counseling among HIV positive young people with non-viral suppression 6 months after initiation of first-line ART in Uganda.

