#### Interventions

##### Group support psychotherapy (GSP)

The content of the GSP has been described in previous publications (29, 30). GSP sessions for caregivers will proceed as previously described in the SEEK-GSP trial (20). GSP sessions for the young people will follow the same format but with a focus on challenges faced by young people living with HIV and will be delivered using play materials. Besides being gender specific, they will also be age specific with participants being grouped into the following age categories: 10–13; 14–16 and 17–18) GSP will be delivered in eight weekly sessions, each lasting 2–3 h. Participants will be divided into sex-specific groups of 10–12 participants. The groups will be closed-meaning that once the group is formed and therapy initiated no other participant can join the group. Trained health workers of the same sex as the group participants will deliver the intervention material following a scripted manual.

The first session addresses issues related to introductions, the group process, expectations, and ground rules and making a pledge to commit to all sessions. Simple games will be used to explain concepts and help the young people get to know each other's name.

The second session will use pictures and practical demonstrations with balloons, to explain the presentation and consequences of abnormal emotions such as persistent sadness, fear, anxiety and anger and how they relate to living with HIV. Thereafter, participants will be asked to communicate with peers and share newly learned knowledge.

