##### Standard of Care—Intensive Adherence Counseling

Both the World Health Organization (WHO) and the Ugandan ART guidelines recommend that asymptomatic persons living with HIV who have been identified with viral load (VL) ≥1,000 copies per ml should be offered Intensive Adherence Counseling (IAC) for 3–6 months (see Table 1) and repeat VL testing before switching to second-line therapy (32). Individuals with detectable viral load 6 months after initiating ART are invited to participate in IAC in the clinic, which consists of at least four sessions with an HIV care provider. Key messages in each counseling session are summarized below.

**Table 1 T1:** Intensive Adherence Counseling Guide

Guide	Components

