## Results

### Trial status

The trial has been approved by the Makerere School of Health Sciences Research Ethics Committee, and the Uganda National Council of Science and Technology. Recruitment began in June 2021 and closed October 2021. A total of 120 young people (10–18 years) living with HIV with their adult caregivers were recruited into the trial. They were randomized to receive the adolescent group support psychotherapy (A-GSP) and intensive adherence counseling (IAC) (*N* = 61) and IAC alone (*N* = 60). An analysis of baseline, 6 and 12-month data is in progress. The results of this trial will be presented at national and international conferences. Manuscripts will be prepared for publication in peer-reviewed journals and reports will be prepared for submission to the funding agency.

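### The 12-group t test rests on a comparator this trial does not have and on control clusters the protocol never defines

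*Protocol article*

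**What the plan says.** The planned arms are "GSP plus IAC (*N* = 60) or IAC alone (*N* = 60"), allocated individually. The Abstract says the primary outcomes will be "analysed by intention to treat using cluster-adjusted t tests and permutation tests".

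The Quantitative data section gives the reason for a cluster analysis: "Although randomisation to GSP and GHE will be done at the individual level, study participants will receive their respective interventions in groups (clusters"). It then takes cluster-level summaries with a Stata collapse command, states that "This procedure will reduce the data from 120 individual participants to 12 groups", and compares cluster means between arms with a t test.

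The two interventions are described differently:

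- **GSP** (Group support psychotherapy section): closed, sex-specific groups of 10–12. "Besides being gender specific, they will also be age specific with participants being grouped into the following age categories" 10–13, 14–16 and 17–18.
- **IAC** (Standard of Care section): clients "are invited to participate in IAC in the clinic, which consists of at least four sessions with an HIV care provider". Table 1 is written for one client, covering that client's own viral load result, adherence score, barriers and plan.

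**The concern.** The sentence that justifies the cluster analysis names a comparator, GHE, that appears nowhere else in the article and is not an arm of this trial. It also says that both arms are delivered in groups. The sections describing the interventions support that for GSP only.

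The unit of analysis, the number of units and the test are therefore fixed on a premise that does not describe this trial's control arm. Half of the 12 units have no stated definition. Adherence and viral load are listed as primary outcomes in Table 2, so the p-value on both would rest on a choice of control grouping made at analysis. The permutation tests named in the Abstract would need the same missing identifiers if they permute clusters.

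**Working it through.** **1. Reproduce the figure of 12.** 120/10 = 12. Also 2 sexes × 3 age bands × 2 arms = 12. The GSP arm alone gives 60/12 = 5 to 60/10 = 6 groups. (Trial status reports 61 in this arm; groups of at most 12 then require six.) So 12 − 6 = 6 units must come from the IAC-only arm. No section says how they are formed. The five clinics mentioned under Limitations would give 6 + 5 = 11, not 12.

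**2. Does the choice of control grouping matter?** The article gives no effect size or intra-cluster correlation (ICC), so the outcomes here are assumptions. Controls: 14/60 suppressed, close to the 23% after IAC cited in the Introduction. GSP: 24/60, with 2, 5, 4, 6, 3 and 4 suppressed per group of 10 (mean 0.400, variance 0.0200). The data stay fixed and only the control grouping changes.

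For 6 versus 6 groups, t = (0.400 − 0.233)/√(pooled variance × 2/6), with 10 df.

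- Even split (2, 2, 2, 2, 3, 3): variance 0.00267, pooled 0.01133, standard error 0.0615, t = 2.71, p = 0.022.
- Uneven split (0, 1, 2, 3, 3, 5): variance 0.03067, pooled 0.02533, standard error 0.0919, t = 1.81, p = 0.100.
- 20,000 random 6 × 10 splits: median p 0.053, central 95% range 0.022 to 0.134, below 0.05 in 36% of splits.
- Five clinics of 12 controls (assumed equal): p = 0.032 for an even spread, 0.080 for an uneven one (1, 2, 2, 4, 5).
- Controls as 60 individuals: p = 0.348 with equal variances, 0.052 with Welch's test.

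In 500 simulated continuous data sets (assumed effect 0.5 SD, ICC 0.05 in GSP, 0 in controls), the central 95% range of p over splits straddled 0.05 in 36%.

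**3. Type I error.** For a random control split fixed in advance, 40,000 runs gave 4.9%, 4.9% and 5.1% at GSP ICC 0, 0.05 and 0.10.

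If controls are instead grouped by sex-by-age cell, any cell differences enter the error term although they cancel in the comparison. Assume unit variance within cells, cell SD 0.4 (variance 0.16) and GSP ICC 0.03:

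- Variance of a GSP group mean apart from cell effects: 0.03 + 0.97/10 = 0.127. Of a control group mean: 1/10 = 0.100.
- True variance of the arm difference: (0.127 + 0.100)/6 = 0.227/6.
- Variance the unpaired test estimates, on average: (0.227 + 2 × 0.16)/6 = 0.547/6.
- Ratio: 0.227/0.547 = 0.41.

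Simulated type I error of the 6-versus-6 t test is then about 0.8%. A nested analysis with individual controls but no sex or age terms reaches only about 1.6%, because the GSP groups still carry the cell differences.

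**4. Degrees of freedom of a partially nested comparison**, at an assumed ICC of 0.05 and six GSP groups of 10:

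- v1 = 0.40 × 0.60 × (1 + 9 × 0.05)/60 = 0.00580
- v0 = 0.233 × 0.767/60 = 0.00298
- Satterthwaite df = (v1 + v0)²/(v1²/5 + v0²/59) = 11.2

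**The case against.** **The article does not say that IAC is individual.** A reader might infer from the Standard of Care section that the control arm has no groups. The text does not settle it. The Quantitative data section asserts groups in both arms. AE management speaks of every group meeting alongside both arms, and Table 2 counts attendance at all eight sessions of either intervention, while the Standard of Care section gives IAC at least four. This objection stands: the supportable statement is that the article contradicts itself and defines no control cluster.

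**The test could be run.** Sex-by-age cells in each arm give exactly 12 units by a deterministic rule, and nothing proposes random re-partitioning. That is fair, but the rule is not stated. Cells of individually counselled controls would also be strata, not units of shared delivery.

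**The illustration is chosen near p = 0.05.** This also stands. With assumed GSP counts of 4, 4, 5, 5, 4 and 4, 98% of splits fall below 0.05. The figures show that the result can depend on the grouping, not how often it will.

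**It is a pilot, and an analysis plan may give the detail.** Limitations does make feasibility and acceptability the major goal, and no power is claimed. But the article does not leave the matter open: it fixes the unit, the count and the commands on a wrong premise.

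**Conclusion.** The point holds as a wrong premise and an undefined unit of analysis. GHE is an error on the face of the text, and about six of the 12 units have no definition. On one assumed data set, the control grouping alone moved p between 0.022 and 0.134. All outcome values, ICCs and the cell SD are assumptions.

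Two stronger readings are not supported:

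- **More false positives.** With a grouping fixed in advance, type I error stays near 5%. With sex-by-age control cells it can fall well below 5%, which costs power.
- **Too few degrees of freedom, or no usable ICC.** The 12-group test has 10 df and the nested alternative about 11, so df is no argument between them. Collapsing the data for a test does not prevent an ICC from being estimated from the same individual records. The Introduction says only "Data will be used to design a definitive cluster randomized trial", without naming the cluster.

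**What to change.** 1. Replace GHE by IAC in the Quantitative data section.
2. Reconcile the sections that describe how IAC is delivered: Quantitative data, Standard of Care with Table 1, AE management and Table 2.
3. If IAC is individual, replace the 12-group t test by a prespecified partially nested analysis. It should have clustering by therapy group in the GSP arm only, controls as individuals, unequal variances, Satterthwaite or Kenward-Roger df, and adjustment for sex and age band. The adjustment is needed because the GSP groups are formed by those factors. State the unit for the permutation tests in the same place.
4. If IAC is in fact given in groups, define the control cluster identifiers before outcomes are compared. The cluster-level test can then stay.

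Trial status says that analysis is in progress, so the choice should be dated and documented before the arms are compared.

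The cost is wording and code, with no new data. The downsides are somewhat more analysis work and still few df, about 11 at an assumed ICC of 0.05.

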#### Randomisation and masking

Randomisation will be done by urn randomisation picked by each participant. The young males and females will be separated into two groups. Each group will be presented with pieces of paper in opaque envelopes whereby half the number of papers will be marked X and the other half Y. Each member of the group will be asked to each pick one envelope. Individuals who pick papers with X will be assigned to both GSP and IAC while those who picked papers with Y will be assigned to IAC only. The same process was repeated for the caregivers.

By design, both experimental and control interventions will be identifiable to participants but will be masked to independent outcome assessors, and data analysts.

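### The planned t test of 12 group means uses neither sex, within which arms are drawn, nor the baseline outcome values, so its intervals are wider than needed if either is prognostic

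*Protocol article*

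**What the plan says.** The Quantitative data section sets the outcome method: "We will apply ttests to cluster-level summaries, which is a robust method of analysis for cluster data". It collapses individual data to group summaries: "This procedure will reduce the data from 120 individual participants to 12 groups". It then uses a named Stata "command to compare cluster means across treatment groups". The abstract describes the primary outcomes as "analysed by intention to treat using cluster-adjusted t tests and permutation tests". Neither place names a stratum or covariate.

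Four other parts of the article bear on this:

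- Randomisation and masking: "The young males and females will be separated into two groups", and each sex draws from envelopes that are half one arm and half the other. Sex is therefore a stratification factor.
- Group support psychotherapy (GSP): groups are single-sex. Of the young people's sessions it says "Besides being gender specific, they will also be age specific", with three age bands.
- Table 2: adherence and viral load are collected at months 0, 6 and 12, and the psychosocial scales at months 0, 2, 6 and 12.
- Quantitative data: baseline values serve to compare arms, to compare completers with non-completers, and to impute missing values. No outcome comparison is said to use them.

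**The concern.** The error term of a t test on group means is the variation between groups within an arm. If groups are single-sex and the sexes differ on the outcome, that difference sits in the error term. But the draw within sex balances sex across arms, so the same difference contributes almost nothing to the error in the arm contrast. The planned standard error then counts variation that the design has already removed. Likewise, chance variation in baseline values stays in the group means although it has been measured.

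Two things are at stake. One is the precision of the preliminary effect estimates. The other is the use made of the variance estimates: the Sample size justification says the pilot is to supply parameters for the main trial's calculation, and an ICC taken from unadjusted group means would mix sex differences with true group correlation.

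**Working it through.** **The plan's own figure.** 120 participants / 10 per group = 12 groups, the lower end of the stated group size of 10 to 12. Also 2 arms × 2 sexes × 3 age bands = 12. The stated 12 reproduces. The 60 per arm comes from a rule of thumb, so there is no power calculation to reproduce.

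**Inputs**

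- From the article: 12 groups, 10 per group.
- Assumed: six groups per arm, three male and three female in each.
- Assumed: ICC 0.05 (range 0 to 0.10), sex difference δ of 0 to 0.5 SD, baseline-outcome correlation r of 0 to 0.6. The article gives none of these.
- Unit: the within-sex SD of the outcome.

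**Formulas**

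- 95% half-width = t(df) × √(2V/6), with t = 2.228 (10 df), 2.262 (9 df), 2.306 (8 df).
- Variance of a group mean, sex aside: V = ICC + (1 − ICC)/10 = 0.05 + 0.095 = 0.145.
- Unadjusted, with three groups of each sex per arm: add (6 × δ²/4)/5 = 0.3δ², on 10 df.
- Sex-adjusted: that term goes, on 9 df.
- Sex and individual baseline: V = ICC + (1 − ICC)(1 − r²)/10, on 9 df.

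**Results at ICC 0.05**

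- δ = 0.3, unadjusted: V = 0.145 + 0.027 = 0.172; half-width 2.228 × √(0.344/6) = 0.534.
- Sex-adjusted: 2.262 × √(0.290/6) = 0.497, a change of −6.8%.
- Sex and r = 0.5: V = 0.05 + 0.095 × 0.75 = 0.12125; half-width 0.455, a change of −14.8%.
- δ = 0.5, unadjusted: V = 0.145 + 0.075 = 0.220; half-width 0.603. Sex and r = 0.5 gives 0.455, a change of −24.6%.
- δ = 0 and r = 0: 0.490 becomes 0.497, a change of +1.5%. With 8 df it is 2.306/2.228 = 1.035, or +3.5%.

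**Sensitivity to the assumed ICC (change in half-width, 9 df)**

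| ICC | δ = 0.3, sex only | δ = 0.3, r = 0.5 | δ = 0.5, r = 0.5 | neither prognostic |
|---|---|---|---|---|
| 0 | −9.9% | −22.0% | −33.5% | +1.5% |
| 0.05 | −6.8% | −14.8% | −24.6% | +1.5% |
| 0.10 | −5.0% | −10.8% | −19.3% | +1.5% |

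**Break-even at ICC 0.05.** Adjustment starts to pay at a sex difference of about 0.12 SD. With no sex difference, it pays at a baseline correlation of about 0.21 (one df lost) to 0.32 (two df lost).

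**Coverage by simulation** (6,000 trials per scenario, ICC 0.05). The unadjusted 95% interval covered 95.2% with no sex difference, 96.5% at 0.3 SD and 97.9% at 0.5 SD. The adjusted interval covered about 95% throughout.

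**Effect on a carried-forward ICC.** With true ICC 0.05, the apparent between-group variance is 0.05 + 0.3δ². At δ = 0.3 the apparent ICC is 0.077/(0.077 + 0.95) = 0.075. At δ = 0.5 it is 0.125/(0.125 + 0.95) = 0.116.

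**The case against.** The strongest defence is that a plain t test on group means is simple, unbiased and valid with few groups, and that 12 groups leave little room for covariates. If neither sex nor baseline predicts outcome, the planned interval has its nominal coverage and adjustment makes it slightly wider. The trial is a pilot with no power target, an analysis plan that is not shown could add an adjusted analysis, and the permutation tests in the abstract could be run within sex. All of this stands as a limit on the size of the point. It does not remove it, because the article fixes the outcome method down to the software command and arm is the only factor in it.

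Four stronger readings are tempting and are not supported:

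- **That the planned test is wrong or biased.** It is not. If sex is prognostic it errs on the conservative side.
- **That its intervals are too wide with nothing gained in return.** That depends on prognostic strengths the article does not give. A large loss of power can be produced by assuming strong sex-by-age differences and matched groups in both arms, but age-banded groups are described only for GSP.
- **That baseline adjustment cuts variance by the full r².** Only the within-group part shrinks. At ICC 0.05 the cut is 0.095r²/0.145: 6%, 16% and 24% for r = 0.3, 0.5 and 0.6, not 9%, 25% and 36%.
- **That an ordinary individual-level regression is the remedy.** It would discard the allowance for group correlation that the plan rightly makes. With r = 0.5, the residual ICC is ICC/[ICC + (1 − ICC) × 0.75], which is 0.040 and 0.066 at ICC 0.03 and 0.05. Design effects 1 + 9 × ICC are then 1.36 and 1.59. Dividing 1.96 by their square roots gives 1.68 and 1.55, a true two-sided error of about 9% and 12% in place of 5%.

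**Conclusion.** The point holds as a conditional loss of precision. The stated analysis uses neither the stratification factor nor the baseline outcomes. When these are prognostic, its intervals are wider than the data require and cover more than 95%, and variance estimates passed to the definitive trial absorb sex differences. At an assumed ICC of 0.05 and three groups of each sex per arm, the avoidable width is about 7% to 25% for the combinations shown. If neither factor matters, adjustment costs about 1.5% to 3.5%. No conclusion about bias or invalidity follows. Because the change is to wording only and the possible gain exceeds the possible loss, the adjusted analysis should be the main one.

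**What to change.** Keep the group-level method and adjust it in two stages.

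1. Regress each outcome at the individual level on sex and its own baseline value, leaving arm out. Use log10 viral load as the baseline for both viral load and suppression, since eligibility makes every participant unsuppressed at entry. Use missed days for adherence and the baseline score for each scale.
2. Average the residuals by group and compare them between arms with a t test whose degrees of freedom are reduced for each group-level covariate (9 when sex is the only one). Run the permutation test named in the abstract within sex.

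An individual-level model is acceptable only with a group random effect or cluster-robust variance, together with a small-sample correction to the degrees of freedom. Report the unadjusted group-level t test as supportive.

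The cost is analysis wording and one or two of the 10 group-level degrees of freedom, with a slightly wider interval if the covariates turn out not to be prognostic. Adding age band as well should not be automatic: with sex it leaves 7 df, and 2.365/2.228 = 1.06, a 6% widening before any gain. No new data are needed.
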